#### Secondary hypotheses

1.3.3

There will be differences in improvement of carers' and patients' outcome variables between the two SUCCEAT intervention groups (workshop support groups vs. web‐based support groups).Carers participating in the SUCCEAT intervention groups will report a greater reduction of burden (Eating Disorder Symptom Impact Scale: Sepulveda, Whitney, et al., 2008), as well as psychiatric symptomatology (Symptom Checklist 90: Franke, 2002), anxiety (State–Trait Anxiety Inventory: Laux et al., 1981), depression (Beck Depression Inventory II: Hautzinger et al., 2006), HEE (Family Questionnaire: Wiedemann et al., 2002), and unmet needs (Carers' Needs Assessment Measure: Graap et al., 2005) at postintervention (T1) than the carers in the control group. Further, they will report a greater increase of motivation to change (University of Rhode Island Change Assessment Scale: Hasler et al., 2003), positive experiences of caregiving (Experience of Caregiving Inventory: Szmukler et al., 1996), and caregiving skills (Caregiver Skills: Hibbs, Rhind, Salerno, et al., 2015) at postintervention (T1) than the carers in the control group.Carers will report acceptability and satisfaction with the SUCCEAT intervention (SUCCEAT Treatment Satisfaction Questionnaire).Patients whose carers participate in the SUCCEAT intervention groups will show a greater reduction of behavioural and emotional problems (Youth Self‐Report: Arbeitsgruppe Deutsche Child Behavior Checklist, 1998) and perceived HEE (Family Emotional Involvement and Criticism Scale: Kronmüller et al., 2001), as well as a greater increase of Body Mass Index, quality of life (Health‐Related Quality of Life Questionnaire for Children and Adolescents: Ravens‐Sieberer & Bullinger, 1998a, 1998b), and motivation to change (Anorexia Nervosa Stages of Change Questionnaire: Rieger et al., 2002) at postintervention (T1) than the patients in the control group.Outcome variables of the carers participating in the SUCCEAT intervention groups and their patients will remain stable at follow‐up (T2) compared with postintervention (T1).The costs of support (Client Sociodemographic and Service Receipt Inventory: Roick et al., 2001) will be lower for carers (and their patients) participating in the SUCCEAT intervention groups at postintervention (T1) and at follow‐up (T2) than for the carers (and their patients) in the control group.

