### Hypotheses

1.3

The outcome measures are mentioned in brackets. These outcome measures are described in more detail in Table 2 and in Supplement S1.

**Table 2 erv2600-tbl-0002:** Outcome measures of the RCT

Instrument	Abbrev.	Domain	Purpose
General Health Questionnaire (Linden et al., 1996)	GHQ	Psychological morbidity and distress^a^	PO, C
Eating Disorder Examination (Hilbert & Tuschen‐Caffier, 2006)	EDE	ED symptomatology^b^	PO, P
Eating Disorder Inventory‐2 (Paul & Thiel, 2005)	EDI‐2	Various dimensions of EDs^a^	PO, P
Caregiver Skills (Hibbs, Rhind, Salerno, et al., 2015, c)	CASK	Skills to support a child with an ED^a^	SO, C
Experience of Caregiving Inventory (Szmukler et al., 1996, c)	ECI	Experiences in caring^a^	SO, C
Eating Disorder Symptom Impact Scale (Sepulveda, Whitney, Hankins, & Treasure, 2008, c)	EDSIS	Burden concerning caring for a child with an ED^a^	SO, C
Carers' Needs Assessment Measure (Graap et al., 2005)	CaNAM	Unmet needs respective caring^a^	SO, C
Symptom Checklist 90 (Franke, 2002)	SCL‐90	Psychiatric symptomatology^a^	SO, C
Beck Depression Inventory‐II (Hautzinger, Keller, & Kühner, 2006)	BDI‐II	Depressive symptomatology^a^	SO, C
State‐Trait‐Anxiety Inventory (Laux, Glanzmann, Schaffner, & Spielberger, 1981)	STAI	State and trait anxiety^a^	SO, C
Family Questionnaire (Wiedemann, Rayki, Feinstein, & Hahlweg, 2002)	FQ	High expressed emotions^a^	SO, C
University of Rhode Island Change Assessment Scale (Hasler, Klanghofer, & Buddeberg, 2003)	FEVER	Readiness for change^a^	SO, C
Body Mass Index (clinical measures of height and weight)	BMI	Weight status^a^	SO, P
Youth Self‐Report (Arbeitsgruppe Deutsche Child Behavior Checklist, 1998)	YSR	Behavioural, emotional problems^a^	SO, P
Health‐Related Quality of Life Questionnaire for Children and Adolescents (Ravens‐Sieberer & Bullinger, 1998a, 1998b)	KINDL	Quality of life^a^	SO, P
Family Emotional Involvement and Criticism Scale (Kronmüller et al., 2001)	FEIWK	Perceived HEE^a^	SO, P
Anorexia Nervosa Stages of Change Questionnaire (Rieger, Touyz, & Beumont, 2002, c)	ANSOCQ	Readiness to recover from AN^a^	SO, P
SUCCEAT Treatment Satisfaction Questionnaire		Feasibility and acceptability of the SUCCEAT intervention	C, Process evaluation
Client Sociodemographic and Service Receipt Inventory (Roick et al., 2001)	CSSRI	Cost‐effectiveness	C, P Economic evaluation

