### Outcome measures

2.4

To describe the sample, clinical data and demographic information about the patients and their carers are collected at baseline (T0; age, sex, educational level, family situation, migration status, and socio‐economic status). Further assessments for the primary and secondary outcome measures (see Table 2) will take place before starting the intervention (T0), after 3 months (postintervention, T1), and 1 year after the intervention (follow‐up, T2). The semistructured interview of the Eating Disorder Examination (Fairburn & Cooper, 1993; German version: Hilbert & Tuschen‐Caffier, 2006) is conducted face‐to‐face or via telephone by professionals (clinical and health psychologists and psychotherapists). These professionals also administer the other questionnaires, which are answered in a paper–pencil version by the carers and patients themselves. These professionals have already been trained to use these measures before this RCT (by experienced professionals in this field) or received training by [name] prior to the study. The questionnaires for the process evaluation are answered by the carers of the SUCCEAT intervention after each workshop session or web‐based module and at T1 and T2. Table 2 and Supplement S1 contain further information about the questionnaires.

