### Sample size calculations

2.5

Power analysis was done with G*Power version 3.1.5. In order to detect a difference for the primary outcome (General Health Questionnaire, see Sepulveda, Lopez, Todd, et al., 2008) by calculating repeated measures analysis of variance (ANOVA; if the s*phericity* assumption is not met) at a 5% significance level with 0.88 power, carers of 40 patients per group are needed to detect medium effects (Faul, Erdfelder, Lang, & Buchner, 2007). We expect a dropout rate of about 17% (see Wagner et al., 2015). Therefore, we plan to include the carers of 48 patients per treatment arm, resulting in a total sample size of 144.

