### Randomisation

2.6

After recruitment of the patients and their carers (at the Medical University of Vienna, Department of Child and Adolescent Psychiatry, and by consultant child and adolescent psychiatrists in adjacent federal states to Vienna), patients and carers who meet the eligibility criteria give their informed consent, perform baseline assessments, and are randomly allocated to one of the two intervention groups (SUCCEAT workshop support group or SUCCEAT web‐based support group) by our research group at the Medical University of Vienna. Random allocation is made in a blockwise manner in order to keep the sizes of treatment groups similar. Incoming patients are numbered consecutively, and randomisation is done blockwise according to the consecutive numbering, in blocks of eight participants in the workshop support group and web‐based support group, respectively. The control group is not randomised.

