### Statistical analysis plan

2.8

The treatment effect will be analysed by using mixed‐design ANOVAs. The time points will be included as within group factor, and the group (workshop support group vs. web‐based support group vs. TAU) will be included as between group factor. *t* tests for dependent and independent samples will also be used in order to explore differences between specific groups and specific time points.

Two analysis strategies will be applied to account for missing data: Intention‐to‐treat analysis will be used as the primary analysis strategy. If posttreatment or follow‐up data are missing, the last‐value‐put‐forward method will be used. Additionally, the analyses will be repeated by including completers only. Completers will be defined by attending more than 50% of the workshop sessions or web‐based modules. To analyse the potential effect of treatment moderators, additional ANOVAs will be calculated including patient's age and duration of illness as covariates.

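### BMI is stated without an age or sex reference in 10–19-year-olds, so an unchanged BMI over the year to T2 would be read as maintenance when it is a decline relative to peers

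*Protocol article*

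**What the plan says.** The patient hypothesis in section 1.3.3 (Secondary hypotheses) expects, at T1, "as well as a greater increase of Body Mass Index" in the intervention groups than in the control group. Table 2 (section 1.3) lists the measure as "Body Mass Index (clinical measures of height and weight", with weight status as its domain and a secondary, patient-level purpose. The superscript on that domain refers to the footnote for self-report measures.

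Section 1.3.3 also contains one general maintenance hypothesis covering every carer and patient outcome in the intervention groups: "and their patients will remain stable at follow‐up (T2) compared with postintervention (T1". No margin and no reference scale are given. Section 2.4 times the assessments before the intervention, "after 3 months (postintervention, T1), and 1 year after the intervention (follow‐up, T2".

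Patients are 10 to 19 years old (section 2.2.1). On the comparator, section 2.6 says: "The control group is not randomised". The main analysis in section 2.8 is a mixed-design ANOVA with time and group as factors. Age appears only in moderator analyses: "additional ANOVAs will be calculated including patient's age and duration of illness as covariates". Sex is not mentioned there.

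**The concern.** Between 10 and 19, expected BMI depends on age and sex. One BMI value therefore describes a different weight status at 11 and at 18, and part of any rise over time is ordinary growth. Without an age and sex reference, the number does not directly measure the weight status that Table 2 names as its domain.

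The two BMI hypotheses are exposed differently. The T1 hypothesis compares groups over 3 months, so growth shared by the groups drops out. The T2 hypothesis looks within the intervention groups over about a year, and nothing drops out. A patient whose BMI has not moved while peers have grown has fallen behind, yet the natural reading of the hypothesis is that the gain was maintained. At stake is how one secondary outcome is read. Among the primary and secondary outcomes in Table 2, it is the only one taken from a physical measurement.

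**Working it through.** **The plan's own figure.** The article gives no numerical target for BMI. Its only power statement, "at a 5% significance level with 0.88 power, carers of 40 patients per group are needed to detect medium effects", concerns the carers' General Health Questionnaire. Reading medium as f = 0.25 (an assumption), with 3 groups, 3 time points, N = 3 × 40 = 120 and the multivariate repeated-measures test of the group-by-time interaction:

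- λ = 0.25² × 120 × 2 = 15, with 4 and 234 degrees of freedom.
- Power = 0.884, which agrees with the stated 0.88. BMI does not enter, so changing its scale leaves the sample size alone.

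**Inputs for the BMI check.**

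- T0 to T1: 3 months = 0.25 year (section 2.4).
- T1 to T2: about 12 months, or nearer 11 if the year is counted from the end of the eight weekly sessions. I use 1 year.
- Peer BMI gain g: assumed 0.2–0.8 kg/m² per year. Not in the article.
- Reference SD: assumed 2–3 kg/m² and treated as constant. Not in the article.

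**T2, within group.** For a patient with exactly unchanged BMI, the shift relative to peers is −(g × 1 year)/SD.

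| Peer gain (kg/m² per year) | SD = 3 | SD = 2 |
|---|---|---|
| 0.2 | −0.2/3 = −0.07 | −0.2/2 = −0.10 |
| 0.4 | −0.4/3 = −0.13 | −0.4/2 = −0.20 |
| 0.8 | −0.8/3 = −0.27 | −0.8/2 = −0.40 |

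The loss is about 0.07–0.40 SD score. The direction holds for any positive growth; only the size depends on the assumptions.

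**T1, between groups.**

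- Growth over the interval: 0.2 × 0.25 = 0.05 to 0.8 × 0.25 = 0.20 kg/m². The part common to the groups cancels in the group-by-time contrast.
- What remains is (difference in growth rate) × 0.25. If growth rates lie between 0.4 and 0.8 per year and the groups sit at opposite ends, this is (0.8 − 0.4) × 0.25 = 0.10 kg/m².
- On the wider 0.2–0.8 range it is (0.8 − 0.2) × 0.25 = 0.15 kg/m².
- A more ordinary imbalance gives far less. If growth falls linearly from 0.8 to 0.4 over the nine years from 10 to 19, a 1-year difference in mean age gives (0.4/9) × 0.25 ≈ 0.01 kg/m².

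**Table 2.** The row describes clinical measurement of height and weight, while its superscript classes the outcome as self-report. The two cannot both be right.

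**The case against.** The strongest objection is that the article does not say BMI will be analysed in kg/m². It says only Body Mass Index, and it sends the reader to Supplement S1 for more detail on the measures. Neither that supplement nor any separate analysis plan is at hand, and either might already standardise BMI. That stands as a limit on certainty. It does not remove the point, because the hypotheses and the outcome definition are stated in the article, on a measure without an age or sex reference.

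Age is also not ignored: the additional ANOVAs take patient's age as a covariate. This gives partial protection for the T1 contrast. They are labelled as moderator analyses and leave out sex. Adjusting for baseline age does not remove average growth from a within-group change between T1 and T2.

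Three stronger readings are tempting, and the documents do not support them.

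- A reader might infer that a 1-year difference in mean age between the groups biases the BMI result by 0.4–0.8 kg/m². That would be a difference in level, and the T1 hypothesis concerns increase. A constant difference in level drops out of the group-by-time contrast.
- A reader might infer that any age or sex imbalance with the non-randomised controls shifts BMI change. It does so only if the imbalance brings different growth rates over those 3 months, and then by little.
- A reader might infer that the article lays down unchanged kg/m² as the criterion of success. It does not. The stability sentence is generic and sets no BMI criterion. The problem is how it would be read when applied to this outcome.

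BMI is moreover a secondary outcome. The primary patient outcomes are the Eating Disorder Examination and the Eating Disorder Inventory-2.

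**Conclusion.** The point holds, mainly for T2. As written, stability of BMI over about a year in patients who may still be growing would be read as maintenance when it is a decline relative to peers. The size is about 0.07–0.40 SD score under the assumed peer gain and reference SD, and least in 17–19-year-olds. At T1 any bias in the comparison with controls is small: about 0.1 kg/m² or less with growth rates of 0.4–0.8 per year, and up to about 0.15 on the wider range. It requires growth rates to differ between groups. Otherwise, including in the randomised workshop-versus-web comparison, the unreferenced scale mainly adds noise. The primary hypotheses are untouched. The self-report superscript in Table 2 is a plain internal contradiction that needs no assumption, but it is separate and editorial.

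**What to change.** Define the weight outcome as an age- and sex-standardised BMI: an SD score, or percent of median BMI for age and sex. Take it from one named reference used at all sites in both countries, and compute it from measured height and weight, sex and exact age at each visit. State the T1 increase hypothesis and the T2 stability hypothesis on that scale, and keep raw BMI as descriptive. If Supplement S1 or the analysis plan already does this, bring section 1.3.3 and Table 2 into line with it. Correct the Table 2 superscript so that BMI is not classed as self-report.

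The cost is a few lines of wording and a reference table. Age and sex are recorded at baseline, later ages follow from the visit dates, and height and weight already underlie BMI, so no new assessment is needed. One limit remains: the last-value rule for missing T2 data in section 2.8 imposes zero change on whichever scale is carried forward, so standardising BMI does not cure that.

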### The SUCCEAT trial aims

1.2

There are three main goals of the SUCCEAT intervention: first, to increase the well‐being of the carers in order to reduce their own risk of developing a mental disorder; second, to support children's and adolescents' recovery from EDs; and third, to attain long‐term changes in the communication within the families to prevent patients from relapsing. A long‐term goal is to provide low‐threshold, cost‐effective, time‐efficient, and transregional support for carers in the future.

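### The secondary hypothesis of stability from T1 to T2 is paired only with tests for a difference, which can refute stability but cannot support it

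*Protocol article*

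**What the plan says.** Section 1.3.3 gives a durability hypothesis for the intervention groups: "Outcome variables of the carers participating in the SUCCEAT intervention groups and their patients will remain stable at" follow-up (T2), with T1 as the reference. It covers all carer and patient outcome variables and does not say how much change would still count as stable.

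Section 2.8 names the analyses. The main one is a mixed-design ANOVA: "The time points will be included as within group factor", with the three groups as the between factor. In addition, t "tests for dependent and independent samples will also be used in order to explore differences between specific groups and specific time points". For missing post-treatment or follow-up data, "the last‐value‐put‐forward method will be used" in the primary analysis.

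Section 2.5 sizes the trial for detecting a difference on the General Health Questionnaire: "carers of 40 patients per group are needed to detect medium effects", "at a 5% significance level with 0.88 power". With about 17% dropout expected, 48 per arm are planned. Sections 1.3.3, 2.5 and 2.8 contain no margin, no equivalence or non-inferiority test and no interval rule for stability.

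**The concern.** The hypothesis is one of no loss, and the tests named are tests for change. A significant T1–T2 difference counts against the hypothesis, but a non-significant one is not evidence for it: it may reflect true stability, a small sample or noisy measurement. If non-significance were used as the criterion, less data would make the hypothesis easier to confirm.

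This is a mismatch between two things that the article itself fixes, the hypothesis and its tests. Apart from costs, section 1.3.3 has no hypothesis comparing SUCCEAT with control at T2, so this is the one hypothesis on how long the clinical outcomes last. At stake is whether a partial loss over the follow-up year could be described as stability.

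**Working it through.** **Inputs from the article.** 40 evaluable and 48 planned per group, 5% significance, power 0.88, a medium effect, 17% dropout (all section 2.5); carry-forward of the last value (section 2.8).

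**Assumptions, not in the article.** Two-sided t tests, T1–T2 correlation r of 0.5–0.7, equal SD at T1 and T2, and the size of the true loss d in SD units.

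**1. The plan's own figure.** Take a medium effect as f = 0.25, with 3 groups, 3 time points, N = 120, and the multivariate group-by-time test, which fits the remark that sphericity may fail. Then λ = 0.25² × 2 × 120 = 15, df1 = 4 and df2 = 2 × (120 − 3 − 2 + 2) = 234. Power is 0.884, against 0.88 stated. For dropout, 40/0.83 = 48.2, against 48 planned. The sample size reproduces, and it is for detecting a difference.

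**2. Chance that a true T1-to-T2 loss is non-significant.** The SD of the change is √(2(1 − r)): 1.00 at r = 0.5 and √0.6 = 0.775 at r = 0.7. The noncentrality of the paired t test is d√n / √(2(1 − r)). For example, d = 0.3, n = 40, r = 0.5 gives 0.3 × 6.325 = 1.90, and P(non-significant) = 0.543. The pooled n is 2 × 40 = 80.

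| True loss | Pooled n = 80, r = 0.5 | Pooled n = 80, r = 0.7 | One format n = 40, r = 0.5 | One format n = 40, r = 0.7 |
|---|---|---|---|---|
| 0.2 SD | 0.576 | 0.374 | 0.765 | 0.643 |
| 0.3 SD | 0.245 | 0.072 | 0.543 | 0.334 |
| 0.5 SD | 0.007 | 0.000 | 0.131 | 0.022 |

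A lower correlation makes this worse. At r = 0.3 a 0.3 SD loss is non-significant in 39% (n = 80) or 65% (n = 40), and a 0.5 SD loss in 4% or 26%.

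**3. Effect of carrying values forward.** A missing T2 replaced by T1 gives a change of exactly zero. With 17% replaced, the expected estimate is 0.83 × d, so a 0.3 SD loss appears as 0.83 × 0.3 = 0.25 SD. In simulation at r = 0.5, the 0.3 SD loss is non-significant in 54% at n = 48 (47% with 48 complete pairs) and in 25% at n = 96 (17% with 96 complete pairs). These rates are about those of analysing only 40 or 80 observed pairs (54% and 25%). The test therefore gains nothing from the filled-in values, while the estimate is biased towards stability.

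**4. What a margin would cost.** For non-inferiority at one-sided 2.5%, with no true change and r = 0.5, power ≈ Φ(margin × √n − 1.96).

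- 0.25 SD margin: Φ(1.58 − 1.96) = 0.35 at n = 40; Φ(2.24 − 1.96) = 0.61 at n = 80.
- 0.3 SD margin: 0.48 and 0.77.
- 0.4 SD margin: 0.72 and 0.95.

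**The case against.** The strongest defence is that nothing in the article says a non-significant T1–T2 test will be taken as proof of stability. Section 2.8 gives the t tests an exploratory purpose, is only two short paragraphs long, and does not assign a test to each secondary hypothesis. An unseen analysis plan could hold a margin or an interval rule. It is also fair to say that the hypothesis refers to the intervention groups together, so the pooled n = 80 is the natural reading; there a 0.3 SD loss is detected in 75–93% of trials and a 0.5 SD loss almost always. The hypothesis is secondary, and the primary hypotheses are set at T1. Finally, the third goal in section 1.2 concerns lasting change in family communication to prevent relapse, which is narrower than stability of every carer and patient outcome.

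Most of this stands as a limit on size. A reader might infer that the trial will declare stability from p > 0.05, or that a moderate relapse would often be reported as stable. The article does not state the first, and the figures do not support the second. What the defence does not remove is that the article pairs a hypothesis of no change with tests that cannot support it and offers no other rule for judging it.

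**Conclusion.** The point holds as a mismatch on a secondary hypothesis. The named tests cannot support the stated stability, and no margin or interval rule stands in for them. The practical risk is an undetected partial loss of about 0.2–0.3 SD, and it is clearly larger when each format is examined alone than when the two are pooled. A loss of 0.5 SD would usually be found: it is missed in under 1% of trials pooled and in 2–13% in one format, at r of 0.5–0.7. The percentages rest on assumed correlations and losses, and they matter only if non-significance is used as the criterion. The carry-forward rule adds a bias towards zero change, but replacing it would not by itself correct the choice of test. The T1 comparisons with control are untouched.

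**What to change.** In sections 1.3.3 and 2.8, state that the T1-to-T2 change in the intervention groups will be reported with its 95% confidence interval, pooled across the two formats first and then by format, from observed or model-based T2 data rather than carried-forward values. Add that stability will not be concluded from p > 0.05.

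A margin is optional. If the investigators want a formal claim of stability, they should fix and justify a margin in advance and make the claim only when the confidence limit excludes a worsening beyond it. The article gives no figure from which to derive a margin, so the choice is theirs.

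The interval-based version changes only wording and reporting and needs no new data. A margin costs more: when it is tight, many outcomes that are truly stable will be inconclusive. At 0.25 SD, for example, the claim would succeed only about 35% of the time in one format and 61% pooled, with no true change and r = 0.5.

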#### Primary hypothesis—Carers

1.3.1

Carers participating in the SUCCEAT intervention groups will report a greater reduction of distress (General Health Questionnaire: Linden et al., 1996) at postintervention (T1) than the carers in the control group.

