#### Study settings and locations where the data will be collected

2.2.2

Patients and carers will be recruited at different inpatient and outpatient centres with ED units, where they receive TAU. Carers and patients who meet the eligibility criteria are invited to participate in the study. Patients and carers both give their informed consent, and parents give their informed consent for children who are minors.

Carers and patients of the two SUCCEAT intervention groups will be recruited at the Medical University of Vienna, Department of Child and Adolescent Psychiatry, and by consultant child and adolescent psychiatrists and at different centres with ED units in adjacent federal states to Vienna. Patients and carers in the two intervention groups give their informed consent and complete the questionnaires at the Medical University of Vienna, Department of Child and Adolescent Psychiatry.

For the control group, patients and their carers will be recruited and receive TAU at three centres: at the Wilhelminenspital in Vienna, Department of Child and Adolescent Medicine, Inpatient and Outpatient Unit for Children and Adolescents; at the Clinical Centre Klagenfurt, Department of Neurology and Psychiatry for Children and Adolescents; and at the Parkland‐Clinic for Psychosomatic and Psychotherapy in Bad Wildungen, Germany. Patients and carers in the control group give their informed consent and complete the questionnaires at the recruiting site.

The interventions started in November 2014 and will continue approximately until April 2018. Follow‐up assessments for the remaining patients are expected to be completed by April 2019. The main ethics approval has been granted by the Medical University of Vienna Ethics Committee (1840/2013). Site‐specific ethics approvals are granted for all participating sites.

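### The cost hypothesis compares cost levels at T1 and T2 with a nonrandomised control group, so a cost difference already present at entry would count as a SUCCEAT effect

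*Protocol article*

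**What the plan says.** **The cost contrast.** Section 1.3.3 says that costs, measured by the CSSRI, "will be lower for carers (and their patients) participating in the SUCCEAT intervention groups at postintervention (T1) and at" follow-up (T2), with the control group as comparator.

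**The other contrasts with control.** The primary carer hypothesis (section 1.3.1) says that carers "will report a greater reduction of distress". The primary patient hypothesis and the secondary carer and patient outcomes compared with control are likewise worded as a greater reduction or a greater increase.

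**The groups.** Sections 2.1 and 2.6 state that only the two SUCCEAT formats are randomised. Section 2.2.2 says: "Patients and carers will be recruited at different inpatient and outpatient centres with ED units, where they receive TAU". SUCCEAT families come through the Medical University of Vienna, consultant child and adolescent psychiatrists, and centres in neighbouring federal states. Control families come from three other centres: one in Vienna, one in Klagenfurt and one in Germany.

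**Schedule and analysis.** Section 2.4 says: "Further assessments for the primary and secondary outcome measures (see Table 2) will take place before starting the intervention (T0), after 3 months" (T1) "and 1 year after the intervention" (T2). Table 2 lists the CSSRI with the purpose "C, P Economic evaluation", without the tag for a primary or secondary outcome. Section 2.8 plans mixed-design ANOVAs with time within and group between. It adds t tests for specific groups and time points, and names patient's age and duration of illness as covariates. It states no model for costs.

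**The concern.** A level comparison after baseline is sound when randomisation makes the groups alike at entry. Here nothing in the design does that for SUCCEAT against control.

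The article also gives reasons to expect service use to differ before entry. The recruiting centres differ, one lies in another health system, and the route through consultant psychiatrists is listed only for SUCCEAT families. Section 2.2.1 adds that the amount of psychological treatment follows need and that some patients are admitted, so service use follows severity and setting.

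Cost-effective support is a stated long-term goal (section 1.2), and section 3.2 promises a conclusion on affordability. If the hypothesis is tested as worded, a saving or a loss could be reported that reflects only where the families were recruited.

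**Working it through.** **1. The plan's own figures.** The article gives no figure for costs. Its sample size is set on the General Health Questionnaire, and it reproduces:
- Multivariate repeated-measures approach, 3 groups by 3 times, N = 120, medium effect taken as f(V) = 0.25: noncentrality 120 × 2 × 0.0625 = 15, df 4 and 234, power 0.884 against the stated 0.88.
- Dropout: 40/0.83 = 48.2, and 48 × 0.83 = 39.8, so 48 per arm is in order. 3 × 48 = 144.

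Only the group sizes are used below.

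**2. The contrasts side by side.**

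| Hypothesis against control | Wording | Uses T0? |
|---|---|---|
| Primary, carers and patients | greater reduction at T1 | yes |
| Secondary, carers and patients | greater reduction or increase at T1 | yes |
| Costs | lower at T1 and at T2 | no |

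**3. What the level contrast estimates.** Let *b* be the mean cost difference, SUCCEAT minus control, at T0. Let *e* be the true effect at T1. Suppose that without an effect both groups would follow parallel courses. Then:
- level contrast at T1 = *e* + *b*
- change contrast (T1 minus T0) = (*e* + *b*) − *b* = *e*

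With *e* = 0 and *b* < 0, the level contrast supports the hypothesis. With *b* > 0 it works against it. The same holds at T2.

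**4. Illustration of size.** The offsets are assumptions, because the article gives no cost means or SDs. Take *e* = 0, a two-sided 5% test, both SUCCEAT groups pooled against control, and a normal approximation:
- SE in SD units = √(1/n₁ + 1/n₂)
- P(significant in the direction of the offset) ≈ Φ(|b|/SE − 1.96)

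| Offset (SD) | 96 vs 48, SE 0.177 | 80 vs 40, SE 0.194 |
|---|---|---|
| 0.2 | Φ(1.13 − 1.96) = 0.20 | Φ(1.03 − 1.96) = 0.18 |
| 0.3 | Φ(1.70 − 1.96) = 0.40 | Φ(1.55 − 1.96) = 0.34 |
| 0.5 | Φ(2.83 − 1.96) = 0.81 | Φ(2.58 − 1.96) = 0.73 |

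Without an offset the figure in either single direction would be 0.025. Costs are usually skewed, so these values show the order of size only.

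**The case against.** **The planned model may already use baseline.** If T0 costs are collected, the group-by-time term of the section 2.8 ANOVA compares change. That is correct, and it makes the remedy easy. But section 2.8 does not tie the cost hypothesis to that term, and the independent-samples t tests at specific time points that it also allows fit the level wording exactly. The hypothesis as written remains the problem.

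**The root is the nonrandomised control, which affects every outcome.** This also stands. Adjustment for T0 needs roughly parallel courses: a group that enters during admissions may see its costs fall anyway. Still, the other hypotheses at least remove the entry difference, and the cost hypothesis does not.

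**Two stronger readings are tempting, and the documents support neither.**
- *That no baseline CSSRI is scheduled.* A reader might infer this because Table 2 does not tag the CSSRI as primary or secondary and the hypothesis names only T1 and T2. But Table 2 presents it among the trial's outcome measures, and it appears in brackets under the secondary hypotheses, which is how section 1.3 identifies outcome measures. The primary hypotheses name only T1 although their measures are taken at T0. Supplement S1, which holds further detail, is not shown.
- *That months between T1 and T2 go unobserved.* No visit is named in that interval, but coverage depends on the CSSRI recall period, which the article does not give. For a 12-month interval the unobserved share is (12 − recall)/12: 75% at 3 months, 50% at 6 months, none at 12 months. A recall period is a detail that an article may leave to its supplement.

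**Conclusion.** The point holds for the wording of the cost hypothesis. It is fixed on levels after baseline, against a nonrandomised control group from other centres and partly another country, with no stated use of costs at entry. Followed as written, it cannot separate an effect of SUCCEAT from a difference that existed before.

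How large the error would be is unknown. The probabilities of 0.20 to 0.81 (96 vs 48) rest on assumed offsets of 0.2 to 0.5 SD, no true effect, an offset that persists, and a pooled comparison. The existence of such an offset is plausible from the recruitment routes but is not shown.

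This concerns a secondary hypothesis. The primary hypotheses, the randomised comparison of the two formats and the sample size are untouched. Whether the CSSRI is taken at T0, and how far it looks back at T2, are items to confirm and not errors.

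**What to change.** 1. **Restate the cost hypothesis as adjusted for T0 service use.** Use either T0 CSSRI cost as a covariate or the group-by-time contrast of the section 2.8 model. Choose one in advance, since the two can differ when groups are not randomised.
2. **Confirm that the CSSRI is taken at T0 in all three groups.** State its recall period at the same time.
3. **Where a T0 CSSRI is missing,** use pre-entry inpatient days from existing site records if they are available. Otherwise report the cost comparison with control as descriptive. Interventions began in November 2014, so a missing T0 form cannot be recovered for families already enrolled.
4. **Say in the report** that adjustment reduces confounding from the nonrandomised control but does not remove it.

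If T0 costs are in hand, the price is a reworded hypothesis and a little more analysis. If they are not, extracting records from several centres in two countries is real work, and the descriptive report is the cheaper course.
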